#### Physical function

Physical function will be assessed via the 5 times sit-to-stand and the 6-min walk test(s). The 5 times sit-to-stand will be conducted by recording the time (in seconds) taken to stand 5 times from a sitting position as quickly as possible. The 6-min walk test will consist of recording the total distance traveled on a flat surface at a self-determined pace in a 6-min period [28].

#### Body composition

Body composition will be assessed via dual-energy X-ray absorptiometry (DEXA) [29]. Assessments of the whole body and appendicular lean mass, in addition to fat mass and bone mineral content, will be obtained. Appendicular lean mass from DEXA and score on the 5 times sit-to-stand will be used to quantify the proportion of individuals who are sarcopenic at pre- and post-intervention, respectively [30].

#### Session effort and dyspnea

Ratings of perception of effort and dyspnea will be recorded for each exercise session. Individuals will be prompted by study staff after every exercise session to record ratings. Specifically, the rating of perception of exertion – effort (RPE-E) scale will be used to assess each participant’s ability to meet the demands of the exercise session [31]. The RPE-E is a single-item scale score from 0 = “No effort” to 10 = “Maximal effort.” Overall dyspnea experience during the session will be assessed using the modified Borg scale-dyspnea (MBS-D). The MBS-D is a scale labeled 0–10, asking participants to rate the best description of their shortness of breath (0 = “Nothing at all” to 10 = “Maximal”) [32, 33]. Participants will be familiarized with scales during the initial study home visits and will be clearly instructed to differentiate these two perceptions when providing ratings.

### Data management

Data collected will be de-identified and coded. Each study participant will have a unique study identification code created following informed consent comprised of two random letters and a consecutive number. Electronic data will be kept in a folder on a password-locked computer in the Department of Exercise Science at the University of South Carolina and only accessible by the investigators and designated research staff. Survey data will be collected using a password-encrypted, online data collection system (RedCap). At the completion of every data collection session, any physical documentation will be stored in a secure filing cabinet with restricted access in a private office in the Department of Exercise Science University of South Carolina. All information will be held in these secure locations (with password protection or key-lock access) and will not be stored external to the university. All paper-based records will be stored in a locked filing cabinet with restricted access in a private office for a minimum of 7 years.

Participants will be provided with an explicit description of plans to share any data they contribute, and how their privacy and confidentiality will be protected. All de-identified data and code for analyses will be made available as soon as possible with publication of the primary outcome paper. The dataset will include demographic information and physiological and psychosocial measures outlined in the proposal. We will make the de-identified data and associated documentation available to users only under a data-sharing agreement that provides a (1) commitment to using the data only for research purposes, (2) commitment to securing the data using appropriate computer technology, and (3) commitment to destroying the data after analyses are completed.

### Statistical analyses

We will use descriptive statistics (percentages and means [with standard deviations]) to report on feasibility outcomes (e.g., recruitment, retention, fidelity). Means and standard deviations will be reported for assessments of exploratory outcomes at baseline and follow-up [18]. Baseline and follow-up testing will be conducted on a per-protocol basis. Descriptive statistics of secondary outcomes will be reported and used to inform sample size calculations for a future randomized controlled trial and aid in decisions on whether their inclusion in future trials is warranted [18, 34]. Analysis will be performed with raw data and code shared on osf.io.

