Cluster sets generally refer to the inclusion of intra-set rest periods (i.e., additional rest during the set itself) [12]. Essentially, cluster sets may allow for reduced levels of fatigue at similar loads of training or enable individuals to perform a greater volume/quantity of training with similar levels of fatigue. Prior research demonstrates that RT with intra-set rest results in the attenuation of fatigue that accompanies consecutive repetition protocols (when training loads are equated), resulting in lower perceptions of effort in comparison to traditional configurations [13–15]. Thus, there is potential for cluster sets to result in lower levels of dyspnea and fatigue, which could facilitate greater exercise tolerance and adaptations in physical function and symptom clusters in individuals with lung cancer.

Home-based exercise is a promising strategy to overcome traditional barriers of facility-based exercise interventions (e.g., resources, travel, cost, limited hours) [16]. We hypothesize that a hybrid approach of delivering exercise programming both in-person and through video conferencing (i.e., live delivery of program via video conferencing) may address some of the anticipated barriers. The initial presence of an exercise professional could help with the delivery of safe and appropriate exercise, whereas the transition towards a hybrid approach could foster independence and autonomy. Furthermore, the impact of COVID-19 has necessitated creative solutions to traditional in-person training, whereby the hybrid delivery approach can help ensure safe exercise, but also limit risk in a potentially vulnerable group [17].

The aims of this study are to (1) conduct a single-arm study to evaluate the feasibility of a hybrid delivery home-based RT program by measuring recruitment, retention, acceptability, and intervention fidelity among survivors and (2) gather data using a pre-/post-test design, to estimate preliminary intervention effects on (a) reducing sensations of dyspnea and (b) improved fatigue, physical function and body composition, and quality of life among survivors immediately post-intervention.

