## Methods/design

This is a single-arm feasibility trial evaluating the effects of an 8-week hybrid delivery of RT with individuals treated for NSCLC. The primary outcome of feasibility will be assessed via recruitment, retention, and intervention fidelity (outlined below). Additional outcomes include health/wellness (dyspnea, fatigue, quality of life), muscular strength (5 repetition maximum and 5 times sit-to-stand), body composition (dual-energy X-ray absorptiometry), and exercise capacity (6-min walk test). Outcomes will be assessed pre-/post-intervention. A convenience sample (*n* = 15) will be recruited to determine the feasibility of the intervention. The sample size was determined based on the recommendations from Julious et al. that justify a minimum of *n* = 12 based on feasibility, gains in precision surrounding the mean and variance, and ability to estimate parameters for future studies [18]. Consequently, in line with other exercise oncology trials and in anticipation of an ~75% retention rate, we aim to recruit 15 individuals to participate. The trial is under review at clinicaltrials.gov and deviations to the protocol or trial procedures will be reflected there and reported in the final manuscript. This study is approved by the University of South Carolina’s Institutional Review Board (Pro00110261). An overview of the study scheme is presented in Fig. 1.

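### Means and SDs at each time point do not match the aim of estimating pre/post effects; the paired change, its interval and the pre-post correlation should be added

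*Protocol article*

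**What the plan says.** The aims at the end of the Background include one on effects: to "gather data using a pre-/post-test design, to estimate preliminary intervention effects on (a) reducing sensations of dyspnea", followed by fatigue, physical function, body composition and quality of life.

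The Statistical analyses section fixes the output for these outcomes: "Means and standard deviations will be reported for assessments of exploratory outcomes at baseline and follow-up". It adds "Baseline and follow-up testing will be conducted on a per-protocol basis" and then gives the intended use: "Descriptive statistics of secondary outcomes will be reported and used to inform sample size calculations for a future randomized controlled trial". It closes with "Analysis will be performed with raw data and code shared on osf.io".

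Methods/design justifies the sample size by a recommendation said to "justify a minimum of *n* = 12 based on feasibility, gains in precision surrounding the mean and variance, and ability to estimate parameters for future studies", and continues: "in anticipation of an ~75% retention rate, we aim to recruit 15 individuals to participate".

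The article nowhere names a within-person change, an SD of change, a confidence interval or a pre-post correlation.

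**The concern.** A pre/post effect is a within-person quantity. Two separate summaries, one per time point, describe the group before and after. They do not say how variable the individual changes were or how precisely the average change is known. The article therefore states an aim of estimation and an output that carries no measure of precision for the estimate. Its own sample size argument rests on precision and on estimating parameters for later studies.

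Two uses are affected. A reader of the results could not judge whether an observed average change is distinguishable from none. The team planning the randomized trial would also lack, in the reported results, the correlation that a baseline-adjusted or change-score calculation requires, although this study collects the data to estimate it.

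**Working it through.** **Inputs from the protocol article.** Minimum n = 12, recruited n = 15 and retention of about 75% (Methods/design); one arm with two assessments; mean and SD at each assessment (Statistical analyses).

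**Assumptions.** The article gives no SD, correlation, effect size, alpha or power for the later trial. I take equal SDs at the two times, r = 0.5, 0.7 and 0.8, and, for the randomized trial, a standardized difference of 0.5, two-sided alpha 0.05 and 80% power.

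**1. The plan's own figure.** 12 / 0.75 = 16, and 12 x 1.25 = 15. The stated 15 is reproduced to within one participant. Expected completers are 15 x 0.75 = 11.25, so I use 11.

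**2. Point estimate of change.** If the same people contribute at both times, the difference of the two means equals the mean paired change exactly. If the baseline mean covers all 15 and the follow-up mean covers 11, the baseline mean is shifted from that of the completers by 4/15 = 0.27 of the baseline gap between dropouts and completers. The article does not say which baseline set is used.

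**3. Precision of change.** In general, SD of change = √(SD₀² + SD₁² - 2r·SD₀·SD₁). With equal SDs this is SD·√(2(1 - r)). The 95% half-width is t(n - 1) x SD of change / √n. For n = 11, t(10) = 2.228 and 2.228/√11 = 0.672. The planned table supplies SD₀ and SD₁ but not r.

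**4. Later randomized trial.** An analysis of follow-up values alone needs 63 per arm at any r. A baseline-adjusted analysis multiplies the variance by 1 - r².

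| Assumed r | SD of change / SD | 95% half-width, n = 11 (in SD) | 1 - r² | Baseline-adjusted n per arm |
|---|---|---|---|---|
| 0.5 | 1.00 | 0.67 | 0.75 | 48 |
| 0.7 | 0.77 | 0.52 | 0.51 | 33 |
| 0.8 | 0.63 | 0.42 | 0.36 | 23 |

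Over a wider range of r, from 0.3 to 0.9, the n per arm runs from 58 to 12 with baseline adjustment and from 88 to 13 with change scores.

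**5. How well 11 completers estimate these inputs.** The 95% CI for an SD on 10 degrees of freedom is the estimate times √(10/χ²), with χ² taken at its 97.5% and 2.5% points. The factors are 0.70 and 1.75. For the correlation, Fisher's z with standard error 1/√(11 - 3) gives -0.14 to 0.85 for an observed 0.5, and 0.17 to 0.92 for an observed 0.7.

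**The case against.** A reader might infer that the plan cannot meet its second aim, that it discards the pairing, or that it cannot yield a usable size for the randomized trial. The documents support none of these readings.

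- **The aim.** The difference of the two means is the mean paired change when the same completers are used, and the per-protocol sentence points that way. It speaks of testing, however, and does not say that the baseline mean is limited to those completers.
- **The pairing.** The article does not exclude change scores, and raw data and code are to be shared, so the pairs are kept. No independent-samples interval or test is proposed, so the plan should not be judged against one.
- **The later trial.** A follow-up SD alone supports a two-group calculation, and it is conservative relative to a baseline-adjusted one (63 per arm against 58 to 12). Nothing says that the later trial's target difference will come from this uncontrolled change.

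It is also fair to say that these outcomes are exploratory, that the success criteria rest on recruitment, retention and fidelity, and that a correlation from 11 pairs is itself weak. A condensed article may leave table layouts to a fuller document.

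These objections limit the point without removing it. The article goes beyond silence: it names the summary statistics, and they fall short of its own stated aim. Data that others could reanalyze do not replace reporting the estimate the study sets out to make. The weakness of the correlation is a reason to give its interval, not to omit it.

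**Conclusion.** The point holds as a mismatch between a stated aim and a stated output. It is a free improvement and not a flaw that defeats the study. The average change is recoverable under a condition the article leaves unstated. Its precision is not recoverable from the planned summaries: with 11 completers and equal SDs, the same table is compatible with a half-width of 0.67 SD at r = 0.5 or 0.42 SD at r = 0.8. The reported results would likewise leave open a baseline-adjusted sample size multiplier between 0.75 and 0.36 over that range.

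The correlations, equal SDs and later-trial settings are illustrative assumptions. The count of 11 rests on the article's own retention figure. The absence of the SD of change, its interval and the correlation from the stated output can be read directly and depends on none of these. No feasibility criterion is affected.

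**What to change.** In Statistical analyses, keep the planned means and SDs and add, for each exploratory outcome and among participants with both assessments:

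- the number of pairs;
- the mean paired change, its SD and its 95% CI;
- the pre-post correlation with its 95% interval.

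State that the baseline mean used for the change covers those same participants. If a baseline summary of everyone enrolled is also wanted, show it separately.

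Where these figures feed the randomized trial's sample size, show the confidence interval of the SD beside the estimate and say how its imprecision will be allowed for, for example by giving the sample size over a range of SDs and correlations. Several conventions exist, and the choice can be left to the team.

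The cost is a few extra columns computed from data already being collected. No new assessment, participant or design change is needed.

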### Limitations

The study has several limitations worthy of addressing. Notably, we are not recruiting individuals with lung cancer with documented dyspnea and fatigue. Recruiting individuals who have reached a certain threshold of dyspnea and fatigue would be a considerable strength of the study in understanding the feasibility and impact of exercise in individuals with documented impairments. However, we opted against this for several reasons. Firstly, there is limited evidence regarding the feasibility and/or effectiveness of exercise in lung cancer in general [35]. Moreover, there is evidence of RCTs of exercise in lung cancer being terminated due to slow accrual and difficulty recruiting individuals with lung cancer to exercise [36]. For those reasons, we opted for an intentionally broad recruitment pool for this feasibility stage of trial development. The inclusion of individuals who are below a certain threshold for dyspnea is something we will be strongly considering for the next stages of our trial development, should this trial be successful.

### Dissemination

The findings of the proposed study will be published in peer-review journals and presented at relevant national and international scientific meetings. Furthermore, the study findings will be translated into plain language and presented to all participants in addition to interested community partners associated with the investigative team.

## Discussion

The primary purpose of this trial is to assess the feasibility of a hybrid delivery of cluster set RT for individuals previously treated for NSCLC. Publication of this protocol is to enhance the transparency around trial success, outcomes of interest, and to aid in the replicability of our protocol.

Progress in improving exercise capacity and exercise participation in this complex clinical population is likely to be supported through individualized approaches that are patient-focused. This single-arm study will examine the intervention feasibility in individuals with NSCLC. Novel aspects of this trial include (1) the investigation of a hybrid delivery of exercise prescription, combining supervised, home-based sessions and distant video-conferencing sessions, and (2) the inclusion of a method of exercise prescription specifically aimed at reducing symptom burden in NSCLC. Despite the potential applications and health benefits of this program, a number of unknowns remain. Specifically, the cluster set design may be different conceptually to what individuals may perceive in considering participation in a more “traditional” resistance exercise program. As such, it is unclear if this will be a feasible approach to delivering resistance exercise, particularly using the hybrid model of in-person and virtual sessions. Moreover, individuals may not be comfortable with researchers coming to their home to deliver the intervention. We have attempted to address this by offering the alternative of a mutually agreed-upon, safe location. However, we will track reasons for non-participation with a particular focus on comfortability with home visits with the intention that these results may guide the design of similar interventions in the future.

At the completion of this study, we expect to have gathered critical information on the feasibility of a hybrid delivery of cluster set RT to individuals previously treated for NSCLC. Our assessments of recruitment, retention, fidelity, and acceptability will provide important information on whether progression to a randomized controlled trial is warranted. Further, qualitative exit interviews will provide us with important information regarding elements of the trial that need to be revised in accordance with participant feedback.

## Data Availability

n/a
